### Biochemical analyses

#### Urinary Lactulose/Mannitol ratio.

Ultra-high performance liquid chromatography (UHPLC, Shimadzu LC-40D, Kyoto, Japan) coupled to a triple quadrupole mass spectrometer (MS/MS; AB Sciex Qtrap 6500+) will be used to determine the urinary Lac/Man ratio to evaluate the intestinal barrier function as described by Gervasoni *et al.* [46]. The UHPLC separation will be performed using an ACQUITY UPLC BEH amide column (Waters, Milford, MA, USA) and sample preparation will be limited to a “dilute and shoot” method using labelled internal standards (D-Mannitol-1-^13^C,1–1-d_2_ and Lactulose-^13^C_12_, Merck Life Sciences, Darmstadt, Germany) which will provide the highest reliability in terms of reproducibility and accuracy. Due to the low ionization efficiency of these sugars, a comparison between electrospray ionization (ESI) and chemical ionization (APCI) will be conducted.

#### Blood analyses.

Plasma glucose and serum insulin, lipids, hs-CRP and safety markers (creatinine, ALP, AST, ALT, GGT) will be analysed at an ISO 15189−2012 accredited clinical laboratory (National Health Laboratory Services, Groote Schuur, Cape Town) according to standard procedures using a Roche Cobas® e501 analyser (Roche Diagnostics, Basel, Switzerland). Briefly, plasma glucose will be determined using colorimetric assay (Randox, Gauteng, South Africa) and creatinine, ALP, AST ALT and GGT will be measured using colorimetric enzyme assays (Roche Diagnostics, Basel Switzerland). Serum insulin, lipid profile and hs-CRP will be measured using immunochemiluminometric assays (IMMULITE 1000 immunoassay system, Siemens Healthcare, Midrand, South Africa). LDL-cholesterol concentrations will be calculated using the Friedewald equation [47]. The HOMA-IR index will be calculated using fasting plasma glucose and insulin levels according to Matthews *et al.* [48]. Remaining SST and EDTA tubes will be centrifuged, and serum and plasma aliquots will be stored at −80 °C until further analyses and for long-term storage.

Biomarkers of intestinal permeability will be measured in plasma or serum samples in duplicate using commercially available enzyme linked immunosorbent (ELISA) kits. The following targets were chosen for intestinal permeability and will be measured at baseline and following the 45-day intervention:

plasma LPS levels will be assessed using a commercial kit (Thermo Fisher Scientific, Waltham, MA, USA) and a plate reader (Spectramax i3x, Molecular Devices, San Jose, CA, USA).serum LBP, sCD14 and IFABP will be measured using commercially available Sandwich ELISA assay kits (R&D Systems, Minneapolis, MN, USA) using a plate reader (Spectramax i3x, Molecular Devices, San Jose, CA, USA).the kynurenine/tryptophan ratio, which is an indicator of indoleamine 2,3-dioxygenase (IDO) activity, will be quantified using the LC/MS/MS method described by Fuertig *et al.* [49] in plasma samples.

#### Faecal short chain fatty acids.

Short chain fatty acids in stool samples will be determined as described by Zhu *et al*. [50]. Stored stool samples will be thawed, acidified, and homogenized with ceramic beads. After centrifugation, the supernatant will be acidified, spiked with an internal standard, and extracted using diethyl ether. The organic phase will be transferred to a tube with sodium sulphate, vortexed, centrifuged, and dried. The dried extract will then be reconstituted with diethyl ether before being analysed via GC/MS to quantify short-chain fatty acids (SCFAs) such as butyric, propionic, acetic, and valeric acids, both individually and as total SCFAs. The quantification will be performed using calibration curves generated from known standards, allowing for precise measurement in µg/g. The GC/MS system will identify compounds based on retention times and fragmentation patterns, with parameters like ionization voltage and temperature optimized for enhanced sensitivity. An Agilent DB-FATWAX UI column (30m, 0.25 mm, 0.25µm) will be used on a Perkin Elmer Clarus 690 GC, employing electron ionization for mass spectrometry analysis.

#### Faecal microbiota analysis.

Nucleic acids will be extracted using the MagMax Microbiome Ultra kit (Thermo Fisher Scientific, Waltham, MA, USA) on the Kingfisher robotic platform. PCR of the 16S rRNA V4-5 region will be performed and sequenced using 2 x 150 paired-end multiplexed sequencing on the NovaSeq 6000. The DNA extraction and 16S ribosomal RNA metagenomic sequencing will be conducted by [name], Director of the Microbiome and Metagenomics Center, at the University of California, San Diego, USA. All amplicon sequencing data will be analysed using the QIIME2 platform [51]. For these data, all sequence data will be quality filtered and de-multiplexed, followed by DeBlur amplicon sequence variant (ASV) calling to obtain unique sequences, which will be compared against various databases to allow for annotation.

### Storage of samples for future use

Permission to store blood, stool and urine samples at −80 °C for future biomedical analyses, specifically exploring diseases such as gastrointestinal diseases, type 2 diabetes, cardiovascular disease, will be obtained from the participants in separate written informed consent forms. Approval from the Human Research Ethics Committee at the SAMRC and University of Cape Town will be obtained before any additional research is performed on stored blood, stool and urine samples.

#### Data management.

Confidentiality will be strictly maintained. Participant names will be removed from all data, and each participant will receive a unique participant identification number to be used for sample and data analysis on the electronic data management system. Data will be entered directly into the electronic data capturing tool Research Electronic Data Capture (REDCap) [52,53] on secure IT infrastructure with backup features at the SAMRC. Personal data is stored separately from the research data on RedCap. Study team members will receive password-protected permission to access the database as required. The PI will have access to personal data to ensure that individual test results can be communicated to the participants at the end of the trial. A data manager will be responsible for ensuring quality and completeness of the data collected. Data and samples will be stored for 10 years and will be made available upon request.

### Statistical analysis

#### Sample size determination.

The study is powered on the primary study endpoint, the Lac/Man ratio, which is based on the data reported by del Piano *et al.* [40] for a similar treatment period. Considering a mean ± standard deviation (SD) difference in the Lac/Man ratio between treatment and control groups (0.015 ± 0.006 versus 0.021 ± 0.007) after the 45-day treatment [40], significance level of p < 0.05 (two-sided test) and power of 80%, 20 participants per group would be sufficient for our study to detect significant differences. When factoring in a drop-out rate of 25% (5/25), 25 participants were selected per group. In the unlikely event that there is a dropout of greater than 25%, we will recruit additional participants until we meet the required sample size.

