## Discussion

Although BFP has been consumed by humans for centuries [60], to the best of our knowledge, this is the first study to explore the potential effects of regular consumption of BFP on intestinal barrier function and gut microbiota diversity in humans. Further, this study will likely advance our understanding of the relationship between intestinal permeability and cardiometabolic risk in humans. There is limited scientific evidence on the sustained effects of BFP in humans. To date our understanding is based on observational studies or acute studies in healthy participants who received once-off treatments [27,29,30]. The outcomes of the study may stimulate further research exploring the effects and mechanisms of action of BFP, including studies in populations with metabolic and other diseases.

A challenge will be the potential for participants to fall ill and require prescription medication such as antibiotics and anti-inflammatory medication. We used a 25% dropout rate to calculate the required sample size to accommodate for incidence of such illnesses. A further limitation presents the reliance of self-reported data such as health status, dietary intake and adherence to the dietary and lifestyle recommendations prior to the Lac/Man test, which may affect the study outcomes.

As the study population comprises relatively young individuals (aged between 25 and 55 years) without known diseases, this may not be representative of the general population. The selection criteria were chosen to minimise confounding factors due to the small sample size. A further limitation is that participants may be unaware that they have chronic diseases, for example HIV, which can affect intestinal permeability [61]. This study will rely on self-reported HIV status to exclude participants living with HIV, which may be prone to errors. Future studies can explore the effectiveness of BFP in a broader population including participants living with HIV, as well as in participants with metabolic diseases such as type 2 diabetes and hypertension.

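### The drop-out allowance is stated as 25% but works out at 20% (5/25), so the replacement rule, read literally, starts at 13 losses when the 40 evaluable participants needed are already gone at 11

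*Protocol article*

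**What the plan says.** Under Sample size determination, the Protocol article takes day-45 Lac/Man means and SDs from a cited study with a similar treatment period ("0.015 ± 0.006 versus 0.021 ± 0.007) after the 45-day treatment"), a "significance level of p < 0.05 (two-sided test) and power of 80"%, and concludes that "20 participants per group would be sufficient for our study to detect significant differences". It then adds the drop-out allowance: "When factoring in a drop-out rate of 25% (5/25), 25 participants were selected per group".

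The next sentence sets a safeguard: "In the unlikely event that there is a dropout of greater than 25%, we will recruit additional participants until we meet the required sample size".

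The Discussion gives the same rate again when it explains how illness during the trial was allowed for: "We used a 25% dropout rate to calculate the required sample size". The Study design section gives the total as 50, randomised 1:1.

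**The concern.** The rate, the fraction and the enrolled number stand in one sentence and cannot all be right. If 25% is the planning rate, 25 per group is too few. If 5 of 25 is the allowance, the rate is 20%. The Discussion repeats 25%, so it is not an isolated misprint in one line.

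The percentage also drives an operating rule. Replacement is tied to drop-out above 25%, whereas the enrolled number has no reserve beyond 20%. Between the two lies a range in which the trial is below its own required size and the rule as worded does nothing. Participants lost before day 45 have no follow-up value of the primary outcome, because the Lac/Man test is done only at baseline and at the 45-day visit.

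**Working it through.** **Inputs** (all from Sample size determination, apart from the total of 50 from Study design): means 0.015 and 0.021; SDs 0.006 and 0.007; two-sided 0.05; power 80%; 20 evaluable per group; 25 enrolled per group.

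**1. The plan's base figure reproduces.**
- Difference = 0.021 − 0.015 = 0.006.
- Pooled SD = √((0.006² + 0.007²)/2) = 0.00652.
- Standardised difference = 0.006/0.00652 = 0.92.
- Power of a two-sample t-test (non-central t, non-centrality 0.92/√(1/n₁ + 1/n₂), df n₁ + n₂ − 2): 80.95% with 20 per group and 78.8% with 19 per group.

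So 20 is the smallest equal group size that reaches 80%, and it has almost no slack.

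**2. The inflation does not reproduce from 25%.**
- 5/25 = 0.20.
- Enrolment for drop-out rate d is n/(1 − d). For d = 0.25: 20/0.75 = 26.7, so 27 per group, 54 in total.
- For d = 0.20: 20/0.80 = 25 per group, 50 in total. This is the stated enrolment.
- 20 × 1.25 also gives 25, but multiplying up does not leave 20 after a 25% loss: 25 × 0.75 = 18.75.

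**3. Where the replacement rule acts, read literally on the total.** 25% of 50 is 12.5, so the rule first acts at 13 losses.

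| Losses of 50 | Rate | Remaining (40 needed) | Rule acts? | Power |
|---|---|---|---|---|
| 10 | 20% | 40 | no, not needed | 80.95% (20/20) |
| 11 | 22% | 39 | no | 79.9% (20/19) |
| 12 | 24% | 38 | no | 78.8% (19/19) or 78.7% (20/18) |
| 13 | 26% | 37 | yes | – |

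Read per group, the gap is one value wide: 6/25 = 24% leaves 19 and does not trigger, while 7/25 = 28% does.

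**4. How likely the gap is.** If each participant drops out independently with probability 0.25, the rate the plan names, the binomial probability of exactly 11 or 12 losses among 50 is about 25%.

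**The case against.** The strongest reply is that the effect is very small. In the range the rule misses, power is at most 1.3 percentage points below 80% for near-balanced losses (80 − 78.7). This stands. A reader might take the 76.5% that belongs to 18 per group as the cost, but 18 per group is 36 of 50, a drop-out of 28%, where the rule has already acted. Only a lopsided split does worse within the gap: 13 against 25 remaining gives 74.5%, and nothing in the document suggests such a pattern.

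Second, the allowance is also given as a count. If 25% is just a wrong label for 5 of 25, the rule means more than 5 of 25 and acts at the sixth loss in a group, with no gap. This is possible, but the trigger sentence carries only the percentage and the Discussion repeats it, so staff applying the text would use 25%.

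Third, a reader might infer that the authors multiplied 20 by 1.25. The document shows no formula, and 25 follows equally from a correct inflation at 20% with the wrong percentage printed. The origin is not established and does not matter for the correction.

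Fourth, the planned analysis is a mixed effects model under intention to treat, with Lac/Man measured before and after. If the baseline value enters the model, precision may improve. The document gives no baseline-to-follow-up correlation r. Assuming residual variance shrinks by (1 − r²), power with 19 per group would be 80.4% at r = 0.2 and 82.5% at r = 0.3; at r = 0 it stays at 78.8%. A loss of 80% power is therefore not shown for the planned analysis, only for the calculation on which the plan sized itself.

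**Conclusion.** The concern holds as a contradiction in a stated design figure and in the replacement rule tied to it. Five of 25 is 20%; 25 per group leaves 20 only at that rate; 25% would need 27 per group. On the literal reading, replacement does not start at 11 or 12 losses of 50, and power then lies between about 79.9% and 78.7%. These figures assume the plan's means and SDs, an unadjusted t-test on day-45 values and near-balanced losses.

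The document does not support the stronger reading that the trial is materially underpowered. The base size of 20 per group is correct from its inputs, 25 per group is adequate at 20% drop-out, and larger losses are caught by the rule.

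**What to change.** In Sample size determination and in the Discussion, state the drop-out allowance as 20% (5 of 25 per group). Reword the replacement rule to start when more than 10 of the 50 randomised are lost, that is, when fewer than 40 participants in total can have a valid day-45 Lac/Man ratio, and name 40 evaluable in total as the top-up target.

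Use the total, not a count per group. Under Intervention and randomisation, the participants, investigators, analysts and statistician are all blinded to allocation, so the trial team cannot count evaluable participants by group. Modest imbalance within a total of 40 costs little: 22 against 18 gives non-centrality 0.92/√(1/22 + 1/18) = 2.90 and power of about 80.6%.

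The cost is a wording change in two places and one or two extra participants if drop-out falls between 20% and 25%. The article reports recruitment as still ongoing in June 2025, so on its own timeline the rule could be corrected before recruitment closed.

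If the sponsor prefers to keep 25% as figure and trigger with 25 per group, the text should say that power may fall to about 79% before replacement starts.

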#### Statistical analysis.

Results will be presented as means ± SD or medians and interquartile ranges for normally and skewed data, respectively. Non-normally distributed data will be transformed for parametric analysis. Intention to treat analysis approach will be used. A mixed effects model will be used to compare within and between groups (control and BFP) differences in primary and secondary outcome variables adjusting for potential confounders as outlined in Table 1. Data will be analysed using STATA SE (version 17, StatCorp, Texas, USA).

Statistical comparisons for taxonomic differences will be performed using Songbird [54], an experimentally validated, compositionally coherent differential abundance method. Statistical visualization of reference frames from Songbird will be performed using Qurro [55], which forms part of a compendium of PCA/PCoA visualization tools such as EMPress [56] and EMPeror [57], designed for the analysis of microbiome datasets. For longitudinal data we will employ volatility analyses, such as semivariograms [58] and Compositional Tensor Factorization [59], to decompose time-series responses into components acting on different timescales. Using these approaches, we will identify taxa that are associated with Baobab fruit powder supplementation, faecal SCFA production, biomarkers of intestinal permeability (LPS, LBP, sCD14, IFABP) and cardiometabolic parameters including glucose, insulin, lipid profiles, inflammatory markers across intervention groups.

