Improved intestinal permeability and microbial composition may modulate dysglycaemia and possibly weight gain. Studies involving healthy adults showed promising acute effects of Baobab fruit extracts on lowering postprandial glycaemia [27,28], while Coe & Ryan [29] reported a reduced 3 hour postprandial insulin response and Garvey *et al.* [30] reported decreased hunger over the 2 hours post consumption.

Based on the reports on the pre-biotic properties in conjunction with the high fibre and polyphenolic content of BFP, we hypothesise that BFP will decrease intestinal permeability, increase intestinal microbial diversity and subsequently lead to improvements in cardiometabolic risk factors. Accordingly, the aim of this study is to perform a randomised double-blind placebo-controlled trial to examine the effects of consumption of BFP on intestinal permeability in participants living with obesity. As secondary aim we will assess the effects of BFP on gut microbiota and cardiometabolic risk factors, as well as confirm the safety for consumption of BFP in humans.

The objectives of this study are to measure the following changes in response to the 45-day BFP intervention compared to the control group:

changes in intestinal permeability using the urinary lactulose/mannitol (Lac/Man) ratio (primary outcome)changes in blood biomarkers of intestinal permeability (secondary outcomes)changes in the composition and diversity of intestinal microbiota profiles using 16S ribosomal RNA gene sequencing (secondary outcomes)changes in cardiometabolic risk markers including anthropometric measurements (such as body mass index (BMI), waist and hip circumference), blood lipid profiles, fasting glycaemia, insulin resistance, inflammation and blood pressure (secondary outcomes)changes in liver (aspartate transaminase (AST), alanine transaminase (ALT), alkaline phosphatase (ALP), gamma glutamyl transpeptidase (GGT)) and kidney (creatinine) function and gastrointestinal symptoms (safety outcomes)

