## Methodology

### Study design

In this randomised double-blind, placebo-controlled trial, 50 apparently healthy women and men living with obesity will be randomised at a 1:1 ratio into an experimental (BFP) or a control (placebo) group. Both BFP and the isocaloric placebo will be consumed daily for 45 days.

The schedule of enrolment, intervention and assessments is outlined in Fig 1. Prior to and following the 45-day intervention, participants will complete one testing session, during which the primary and secondary outcomes as well as potential confounders will be measured. To assess safety of BFP, liver (liver enzymes) and kidney (estimated glomerular filtration rate, GFR) function will be assessed at baseline, 2-weeks into the intervention and following the 45-day intervention. Gastrointestinal symptoms will be assessed weekly using validated questionnaires. Participants will be monitored weekly by alternating telephonic contact and visits to the research facility to confirm compliance, acceptability and tolerability. Adverse events, such as allergic reactions, and incidence of other potentially confounding health issues such as illnesses that require extended use of medication will also be assessed. The participants will be encouraged to maintain their usual dietary and lifestyle behaviours during the intervention period. Participants will be reimbursed for their time and travel costs. The overview of the study design is described in Fig 2.

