#### Participant recruitment and screening.

Participant recruitment and testing sessions will be conducted at the research facility at the University of Cape Town (UCT) in Newlands, Cape Town, South Africa. Awareness will be raised through sharing advertisements via mailing lists and using social media posts on Facebook, LinkedIn and Twitter. Flyers will be distributed at UCT and in the surrounding community to attract participants who are living close to the research facility. Prior to recruitment into the study, participants will undergo screening to confirm their eligibility.

Participants will be invited to attend a screening visit where the purpose of the study and the procedures will be explained in detail and queries regarding the study will be answered. Participants will then sign the informed consent form if they agree to participate in the study and complete a detailed screening questionnaire listing compliance with inclusion (age between 25 and 55 years, body mass index (BMI) ≥ 30 kg/m^2^) and exclusion criteria as detailed in Table 1. Participants with gastrointestinal diseases, previous gastrointestinal surgery, chronic diseases, those taking chronic medication, smokers, pregnant or breastfeeding women will be excluded (Table 1). Body weight, in lightweight clothing without shoes will be measured to the nearest 0.1 kg using a digital scale (Tanita TBF-410GS Total Body Composition Analyzer, Tokyo, Japan), height will be measured to the nearest 0.1 cm using a wall-mounted stadiometer (Holtain, Ltd., Crosswell, UK) [31,32] and BMI will be calculated as weight (kg)/height (m)^2^. After the participant had been seated for at least five minutes, three blood pressure readings will be taken at two-minute intervals using a digital blood pressure monitor (Rossmax, Heerbrugg, Switzerland). After an overnight (10–12 hours) fast, blood samples will be drawn for the measurement of screening parameters including fasting plasma glucose and serum lipid profile (high density lipoprotein (HDL)-cholesterol, low density lipoprotein (LDL)-cholesterol, total cholesterol and triglycerides). Participants that meet all inclusion and exclusion criteria will be enrolled in the study.

**Table 1 pone.0328774.t001:** Inclusion and exclusion criteria.

	*How is it determined:*	*Motivation:*

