** *Inclusion criteria* **		
Ability to sign informed consent	Confirmation through questions that participants understand what will be asked of them	Ethical requirement.
Age between 25 and 55 years	Date of birth	This younger age group may be at risk but less likely to display co-morbidities or non-communicable diseases associated with obesity, which could be considered confounders.
Body Mass Index (BMI) ≥ 30 kg/m^2^	Anthropometric measurements	BMI above 30 kg/m^2^ has been associated with increased risk for increased intestinal permeability [33,34].
Weight stable (less than 5 kg weight change in the last 6 months)	Self-reported change in clothes size	Weight change affects cardiometabolic risk factors.

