
The intervention and placebo powder were packaged in foil sachets protected from light by Joypak, Cape Town, South Africa, with non-identifiable labels to ensure that both study staff and participants will be blinded to the group randomisation/allocation. Participants will be block randomised at a 1:1 ratio with random permuted block sizes of 2 and 4 while applying *a priori* stratification for sex. Researchers will use the randomisation module on RedCap to allocate a randomisation number to the participants on the day of baseline testing. Participants, investigators, analysts and statistician will be blinded to the group allocation. In the event that unblinding becomes necessary, two independent SAMRC staff members who are not directly involved in the study will be able to identify specific codes.

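### The covariate set is defined by pointing to the eligibility table, which supplies mostly constants, does not limit the items that vary to baseline values, and leaves out sex, the stratification factor

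*Protocol article*

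**What the plan says.** The Protocol article's Statistical analysis section gives one covariate rule for all the mixed models: they compare the groups on "primary and secondary outcome variables adjusting for potential confounders as outlined in Table 1". The article has a single Table 1. The section on participant recruitment and screening introduces it as the list of "inclusion and exclusion criteria", and the same section states that "Participants that meet all inclusion and exclusion criteria will be enrolled in the study".

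Three other places bear on the rule:

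- The objectives in the Introduction list, as secondary outcomes, "changes in cardiometabolic risk markers including anthropometric measurements (such as body mass index (BMI), waist and hip circumference), blood lipid profiles, fasting glycaemia", and go on to name blood pressure.
- Study design says that, at the testing sessions before and after the intervention, "the primary and secondary outcomes as well as potential confounders will be measured".
- Intervention and randomisation describes permuted blocks with "stratification for sex".

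**The concern.** A model can adjust only for something that differs between participants. A table of entry criteria lists, for the most part, things that do not differ among those who got in. Its remaining items are mainly measurements that the trial also treats as outcomes and takes again after randomisation.

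The rule therefore leaves the analyst to decide which Table 1 items enter, and at which visit. The visit matters. A screening or baseline value is a legitimate covariate. A follow-up value of a variable that the intervention is hypothesised to change is not, because conditioning on it can remove or distort part of the treatment effect. The list also omits the one covariate that the design itself singles out, sex. In a trial planned for 20 evaluable participants per group, such choices should not be open after the data are seen.

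**Working it through.** **Step 1: classify the rows of Table 1.** Without the two group headings there are 22 individual rows: 4 inclusion and 18 exclusion.

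| Rows | Count | Variation among those enrolled |
|---|---|---|
| Consent; gastrointestinal disease or surgery; smoking; acute infection; pregnancy or breastfeeding; three medication rows; autoimmune, heart, reproductive, thyroid and infectious disease; stroke; allergy or intolerance; recent antibiotic, fibre or pre-/probiotic use | 16 | None at entry |
| Age; BMI; recent weight change; blood pressure; fasting glucose; lipids with Framingham score | 6 | The underlying measurement varies within the permitted range |

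16 + 6 = 22. Even the six are constant as yes/no criteria; only the value behind them varies. An entry such as "Age between 25 and 55 years" leaves a 30-year range. Recent weight change is marginal, since it is judged from self-reported change in clothes size.

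Some entries in the Motivation column do speak of confounding, but as a reason for restricting entry. The BMI row says that "BMI above 30 kg/m^2^ has been associated with increased risk for increased intestinal permeability". The Discussion confirms that the selection criteria were chosen to reduce confounding. That is control by restriction, not a covariate list.

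**Step 2: set the varying items against the outcomes and the visits.**

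| Item | Secondary outcome? | Measured after randomisation? |
|---|---|---|
| Age | No | Not applicable |
| Recent weight change before entry | No | Not applicable |
| BMI | Yes | Weight every 2 weeks and at day 45 |
| Blood pressure | Yes | Every 2 weeks and at day 45 |
| Fasting glucose | Yes | Day 45 |
| Lipids | Yes | Day 45 |

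Four of the six are outcomes with later values, and the analysis sentence does not say which visit is used. When one of these four is itself the response, the covariate list contains that same variable.

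**Step 3: look for sex.** Sex is not a row. It appears only inside the sex-specific Framingham cut-offs. Diet, physical activity, stress and alcohol, which are collected at the testing sessions, are not rows either.

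**Step 4: scale.** The planned sample size reproduces. The difference is 0.021 − 0.015 = 0.006 and the pooled SD is √((0.006² + 0.007²)/2) = 0.00652, so the standardised difference is 0.92. The normal approximation gives 19 per group. The t-test gives 19.54, so 20, with power 81.0%. That calculation has no covariates.

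The article contains nothing that would size the bias from follow-up covariates or the loss from omitting sex. For orientation only, take the same two-group comparison with 20 per group and add k covariates assumed to have no prognostic value. The noncentrality is 0.006/(0.00652 × √(2/20)) = 2.91. It is divided by √(37/(37 − k)), with 38 − k degrees of freedom:

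| k | 0 | 1 | 2 | 7 | 10 |
|---|---|---|---|---|---|
| Power | 81% | 80% | 79% | 72% | 67% |

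Seven would be age, BMI, systolic and diastolic pressure, glucose, triglycerides and LDL. Prognostic covariates would move power the other way, and the planned mixed model is not this simple comparison. The table shows only that the length of the list is not a trivial choice at this size.

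**The case against.** The strongest defence has four parts.

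- **Timing.** Table 1 has a column on how each item is determined, and BMI, blood pressure, glucose and lipids are measured for it at screening, before allocation. Reading the rule as screening values is natural, and that adjustment causes no bias. This largely stands. A reader might infer that the plan conditions on post-randomisation outcomes, but the text does not say so. It leaves the point open, because Study design has confounders measured at both testing sessions.
- **Constants.** Terms without variation drop out of the fit and leave the estimate unchanged. This stands: those rows are useless rather than harmful.
- **Baseline outcome.** A reader might infer that the plan forgoes baseline adjustment, and put the cost at 20/(1 − r²), or about 22, 27 and 39 per group for assumed correlations of 0.3, 0.5 and 0.7. The article does not support this. Those figures compare with a follow-up-only analysis, whereas the plan is a mixed model for differences within and between groups, which probably already carries the baseline outcome as a repeated response. If that model behaves like a change-score analysis, the gain from covariate adjustment is a factor 2/(1 + r): 1.54, 1.33 and 1.18 at the same correlations. If baseline means are constrained equal, there is essentially no gain. The article does not say which applies and gives no r.
- **An unseen SAP.** A full covariate list is often left to one. That would answer silence. Here the article states a source for the list, and that source cannot supply it.

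**Conclusion.** The point holds as a defective covariate rule, not as a planned bias. The Table 1 reference yields 16 rows that cannot be used and six that can. Four of those six are also outcomes with post-randomisation values, and nothing limits them to baseline. Bias would arise only if follow-up values were entered, which the text permits but does not require.

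Omitting sex leaves the estimate unbiased. Because allocation is balanced within sex, the intervals come out too wide by an amount that depends on how strongly sex predicts the outcome; the article gives no figure for that.

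No overall loss of power can be attached to this point. The power figures for added covariates rest on the assumption that they have no prognostic value, and the conclusion does not depend on them. It rests on the article's own text: the identity of Table 1, the enrolment rule, the outcome list and the stratification factor.

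**What to change.** Replace the reference to Table 1 in the Statistical analysis section with wording such as:

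> All between-group comparisons adjust for sex (stratification factor) and use the baseline value of the outcome once, either as a covariate with day 45 as the response or as a repeated response with baseline means constrained equal between groups. Any further covariates (for example age and BMI) are named in advance and enter at baseline values only. No post-randomisation variable is a covariate.

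The sponsor should choose one of the two baseline options and say which. Adding baseline as a covariate while also keeping it as a response would put it on both sides of the model. Any further covariates should be few, given the planned size.

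The cost is a short change of text, made before unblinding and carried into the SAP if there is one. Sex and the baseline values are already collected, so no new data or visits are needed.
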